### Technological background

The intervention programme named *MOBILE COACH* is fully based on the use of mobile technology. The programme used in the present study is similar to an earlier text-messaging programme for smoking cessation, which was successfully tested in two pilot studies [19]. All outgoing SMSs, videos, audio messages and images will be automatically recorded. All SMSs, images, videos and audio messages will be designed prior to the commencement of the broadcasting period.

### Intervention elements

The intervention programme consists of (1) assessment of the individual knowledge and awareness and practice about childhood drowning, and drowning related attitudes; (2) a weekly SMS and images for the assessment of knowledge, and awareness and practice about childhood drowning; (3) a monthly audio and video assessment of knowledge, and awareness and practice about childhood drowning; and (4) assessment to reduce the incidence of childhood drowning and risk factors for childhood drowning.

### Weekly SMS and images assessment

During the six-month intervention period, participants of the intervention group will receive one SMS and image per week for the assessment of knowledge and awareness and practice about childhood drowning. The weekly SMS and image assessment will be sent at a fixed point in time each week, 9:00 a.m. to 6:00 p.m., because 60 % of drowning events in Bangladesh happen during that time. All intervention participants will receive brief training concerning the use of the SMS and image intervention from the study assistants. On Friday morning of each week, the site study assistants will send an SMS and image to parents in the intervention group to enquire about their status and remind them of the availability of phone based support. The SMS will typically be 150–200 characters long and in Bangla language.

### Monthly audio and video assessment

Participants of the intervention group will receive one audio message and video per month for the assessment of knowledge and awareness, and practice about childhood drowning during the six-month intervention period. All the intervention participants will receive a brief training concerning the use of the videos and audio intervention from the study assistants.

### Control group

The study participants of the assessment only control group will not receive any of the intervention elements of the *MOBILE COACH* described above.

### Data collection method

#### Baseline survey

Fifteen study assistants and two supervisors will collect data from the two selected union parishad (15 villages) intervention groups and two union parishad (15 villages) control groups. The study assistants will home visit and collect data from the parents through face-to-face interviews using a set of pre-tested questionnaires. The baseline survey will be conducted one month before implementation of the respective intervention packages.

#### Injury surveillance

The study assistants for the surveillance areas will collect data by regular household visits at one-month intervals. The surveillance areas will be divided into 6 blocks, each consisting of around 100 to 150 households. For two blocks, one injury surveillance study assistant will be exclusively responsible for collecting data. In the first round of surveillance, the study assistant will be provided with a unique number for each of the households in a systematic manner, and will collect mobile phone numbers from each household. The study assistants will visit each household regularly at one-month intervals using surveillance instruments. Accordingly, they will visit approximately 20 households a day. The study assistants will conduct interviews with the parents of the family. The first time they visit the family, the study assistants will complete the Household Information Form. In each visit, the study assistants will check the injury surveillance system screening form. If any child is born or dies, the respective form will be completed. For each group area, one supervisor, the respective project co-coordinator, will be responsible to maintain the quality of the data.

#### End line survey

The end line survey for the intervention areas will be conducted in the last surveillance round. About 1680 households will be covered by 15 study assistants. Two supervisors will supervise the activities of the study assistants. The end line survey will use the same instruments as those used in the baseline survey and the same procedure will be followed to collect data. The survey will be conducted over 15 days.

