**Method/design:**

A two-arm cluster randomized community trial will be conducted to test the efficacy of the mobile coach intervention for childhood drowning on parents with children below five years of age and compared to an assessment only control group. A total of 1680 parents in the villages with children aged below five years of age will participate. The village will be used as a randomized unit, randomly assigned to an intervention group (*N* = 840) receiving the mobile coach based intervention or an assessment only control group (*N* = 840). An individualized mobile coach intervention based on the demographic data and the individual will be developed, and SMSs, audio messages, videos and images about childhood drowning will be sent to the participants of the intervention group over a period of six months. The participants will receive per week one text message (SMS) and image and one video and audio text per month. The primary outcome measure will be increased knowledge and safety awareness, and behaviour practice about childhood drowning assessed at the six-month follow-up, and the secondary outcome measure will be the reduced incidence of childhood drowning in Bangladesh. The study assistants conducting the baseline and the follow-up assessments will be blinded regarding the group assignment.

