## Method/design

### Design and main hypothesis

A two-arm cluster randomised community trial will be conducted to test the efficacy of the mobile coach based intervention for the prevention of childhood drowning among parents with children aged below five years compared to an assessment only control group. In respect of the childhood drowning knowledge, awareness and practice, SMSs, videos, audio messages and images will be sent to participants based on the Ministry of Health and Family Welfare, Bangladesh Government and Centre for Injury Prevention and Research, Bangladesh. The mobile coach will be sent to the participants over a period of six months and data will be gathered at baseline, with a weekly SMS and images, and monthly videos and audio assessment. The main hypothesis is that the integrated intervention will be a more effective and inexpensive way to prevent childhood drowning among children aged below five years, and also increases the parent’s awareness of their children in respect of drowning. At the six-month follow-up, the primary outcome will be the per monthly increase in knowledge, safety awareness and behavioural practice in respect of childhood drowning prevention of the intervention group compared to those in the assessment only control group. The secondary outcome measures will be reducing the incidence of childhood drowning to compare the baseline and end line assessment with the self-efficacy for childhood drowning prevention, and also to determine the risk factors for childhood drowning. An overview of the study design is presented in Fig. 1.

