### Sample size calculation

The following formulae for hypothesis testing of the two group comparison was used [16] *N* = {Z1 – α/2 √2P̃ (1 – P̃) + Z1 – β √P1 (1 – P1) + P2 (1 – P2)}^2^ / (P1 – P2)^2^. P1 = Proportion of drowning in boy children aged under five years 55 % = 0.55; and P2 = Proportion of drowning in girl children aged under five years 45 % = 0.45 [17]. P̃ = (P1 + P2)/2 = 0.5 and adjusting for 10 % non-response *N* = 392+ 10 % of 392 = 431. A sample size of *N* = 431 in each study group would have 80 % power for a Chi-Square Test (*α* = 5 %, 2 *sided*) in order to detect this difference based on a calculation using G-Power. As union participants are nested within villages, a potential design effect needs to be considered. An assumed number of participants per village of 30 and an intra-cluster correlation coefficient of 0.05 could be expected. This would result in a design effect = 1+ (m-1) × ICC = 1+ (20–1) × 0.05 = 1.95. Multiplying this design effect by the “required size for an unnested sample (*N* = 431)” results in a required sample size of *N* = 840 per study group and a total of *N* = 1680 study participants.

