### Outcomes

The outcomes of the study will be to determine the knowledge, awareness and behaviour practices about childhood drowning, as well as the risk factors, and reduce the incidence of childhood drowning. To determine the knowledge pertaining to childhood drowning, five questions about the knowledge of childhood drowning are provided. The questions will be answered YES or NO. A correct answer will score one mark and a zero mark will be given for an incorrect answer. The participants will be classified as having knowledge of drowning if they correctly answer all five questions. Based on those five questions, the total summated score will be calculated. Five questions will be used to measure the awareness about childhood drowning. Based on the five questions, the total summated score will be calculated. The behaviour practices will be divided into supervision practices and swimming ability. In addition, five questions will be used to measure the behaviour practices. Based on the five questions, the total score will be calculated. The study assistants will conduct the six-month follow up assessment by field interviews. The primary outcome will be the monthly assessment of increased knowledge, and safety awareness and practice about childhood drowning. The secondary outcome will be the assessment of reducing the incidence of children drowning to compare the baseline data and end line data, and also to determine the risk factors for childhood drowning. Finally, the outcome variables will be the effects of the mobile coach Intervention on the community in Bangladesh.

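### The end line survey text contradicts itself on whether controls are surveyed, and the monthly form of the primary outcome has no described control-arm measurement

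*Protocol article*

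**What the plan says.** **Who is surveyed at the end.** The End line survey section opens: "The end line survey for the intervention areas will be conducted in the last surveillance round". The next sentence reads: "About 1680 households will be covered by 15 study assistants". The section then adds: "The end line survey will use the same instruments as those used in the baseline survey and the same procedure will be followed". Under Sample size calculation, the plan's arithmetic "results in a required sample size of *N* = 840 per study group and a total of *N* = 1680 study participants".

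**When the primary outcome is measured.** There are three wordings:

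- The abstract has the outcome "about childhood drowning assessed at the six-month follow-up".
- Design and main hypothesis says that, at six months, "the primary outcome will be the per monthly increase in knowledge, safety awareness and behavioural practice", compared with the control group.
- Outcomes says: "The primary outcome will be the monthly assessment of increased knowledge, and safety awareness and practice about childhood drowning".

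**What controls receive.** The Control group section says that these participants "will not receive any of the intervention elements" of the programme. The sections on intervention elements, the weekly SMS and images, and the monthly audio and video describe these items as assessments of knowledge, awareness and practice. They are sent to the intervention group.

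**The concern.** Two things must be unambiguous for the primary comparison: which parents are interviewed at the end, and at what time the outcome is taken. The protocol gives conflicting answers to both.

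A field team that follows the opening sentence of the End line survey section would visit only the intervention villages. A team that follows the household count would visit both arms. A control interview missed at six months cannot be recovered afterwards.

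An analyst who follows the monthly wording would look for monthly knowledge, awareness and practice data in both arms and find no described source for them in controls. The test named under Data analyses would not expose either problem. It is a paired t-test of pre-test against post-test scores, which can be run without any control end line data.

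**Working it through.** **Step 1: reproduce the planned total.** Inputs from Sample size calculation: proportions 0.55 and 0.45, two-sided 5% level, 80% power, 10% non-response, intra-cluster correlation 0.05, and cluster size 20 as used in the design-effect formula.

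- Two-proportion formula without continuity correction: 392 per arm.
- Non-response: 392 × 1.10 = 431.2, taken as 431.
- Design effect: 1 + (20 − 1) × 0.05 = 1.95.
- Per arm: 431 × 1.95 = 840.45, taken as 840.
- Both arms: 2 × 840 = 1680.

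The stated figures reproduce.

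**Step 2: compare with the end line count.** 1680 ÷ 840 = 2.0. The household count equals both arms exactly. A survey of the intervention areas alone would cover about 840 households, so the two opening sentences of that section cannot both be right.

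**Step 3: check the stated resources.** 1680 ÷ 15 assistants = 112 households each. Over the stated 15 days, 112 ÷ 15 = 7.47, or about 7.5 households per assistant per day. Injury surveillance expects roughly 20 household visits a day, so a two-arm survey fits the plan.

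**Step 4: see whether the link to surveillance settles it.** The end line survey is placed in the last surveillance round. Injury surveillance describes 6 blocks of about 100 to 150 households: 6 × 100 = 600 to 6 × 150 = 900. That range contains one arm (840) but not both (1680), unless the 6 blocks are meant for each group area. The text does not say which, so this section does not resolve the contradiction.

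**Step 5: look for a monthly measurement in controls.**

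| Source | Frequency | Knowledge, awareness and practice measured? | Controls included? |
|---|---|---|---|
| Baseline survey | once | yes | yes, both arms named |
| SMS and images | weekly | described as assessment | no |
| Audio and video | monthly | described as assessment | no |
| Injury surveillance visits | monthly | only surveillance instruments and forms are named | not clear |
| End line survey | once | yes, same instruments as baseline | contradictory |

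No row gives a monthly score in controls. The two rows that could give a comparable score in both arms are the two surveys.

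**Step 6: what the per-month wording could mean.** If it means only the change from baseline to end line divided by the number of months, the two surveys supply it. Dividing every parent's change by the same constant divides the between-arm difference and its standard error by that constant, so the test statistic is unchanged. On that reading the words add nothing. On the other reading, repeated monthly scores, the control data are not described.

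**The case against.** The strongest reply is that the plan as a whole provides for control data at six months, and much of it stands:

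- The household count is the two-arm total.
- The end line procedure repeats the baseline procedure, and the Baseline survey section names intervention and control villages.
- Randomisation and allocation concealment has the follow-up interviewers blinded when they assess the primary and secondary outcomes, which would serve little purpose if only one arm were interviewed.
- Outcomes describes six-month field interviews without limiting them to one arm.
- The comparator is called an assessment-only control group.

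A reader who stops at the opening sentence of the End line survey section might infer that none of the 840 control parents has a post-baseline outcome and that the trial cannot compare its arms. The documents do not support that. The inference needs one phrase to be taken literally and the sentence after it to be ignored.

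A reader might also infer that intervention parents are scored repeatedly through the messages, so that practice with the questions favours that arm. That is not supported either. Technological background says that outgoing messages are recorded, and no reply channel or scoring of replies is described. The sections seem to use the word assessment loosely for content sent to parents.

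The per-month wording under Design and main hypothesis can be read as a rescaled six-month change. The wording under Outcomes, which makes a monthly assessment the primary outcome, is much harder to read that way. The objection therefore removes the claim of missing control data. It does not remove the contradiction over survey coverage or the conflict over timing.

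**Conclusion.** Two contradictions stand:

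1. The End line survey section names one arm and counts two: 1680 households against about 840.
2. The primary outcome is set at six months in one place and monthly in two others, and no monthly knowledge, awareness or practice measurement is described for controls. In the sense of repeated monthly scores, the outcome cannot support the between-arm comparison that the design section promises.

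The likely intent is a six-month interview in both arms. This conclusion rests on reading the household count, the repeated baseline procedure, the blinded follow-up and the assessment-only comparator together. No sample size or resource figure changes. The correction still matters, because the primary comparison depends on who is interviewed and when, and both are set inconsistently in this document. They are not details left to an analysis plan.

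**What to change.** - **End line survey:** state that the survey takes place in both intervention and control areas, with the same instrument and within the same 15-day window.
- **Design and main hypothesis, and Outcomes:** delete the words per monthly and monthly. Define the primary outcome as the knowledge, awareness and practice score at the six-month end line survey, compared between arms with adjustment for the baseline score. This agrees with the abstract.
- **Intervention sections:** state that any responses to SMS, images, audio or video are process data only and do not enter the primary outcome.
- **If a monthly outcome is really wanted:** describe a monthly measurement in controls with the same instrument. That would be new fieldwork, not a wording change.

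The first three changes cost only wording. The planned 1680-household workload already covers both arms.

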#### Study duration

The duration of the study is six months. The activities of the intervention programme will commence in March 2015 and end in August 2015.

### Data analyses

The data will be entered into SPSS statistical package version 22.0.

The proportion, mean and standard deviation will be used to quantify the level of knowledge, awareness and practice before and after intervention.

The paired *t*-test will be used to examine the effectiveness of the intervention programme by comparing the pre-test and post-test score in respect of knowledge, awareness and practice.

The chi-square test will be worked out to determine the association of the socio-demographic, environmental and behavioural factors with childhood drowning.

In addition, the risk factors for childhood drowning with socio-demographic, environmental and behavioural factors will be determined using multivariate logistic analysis.

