### Randomisation and allocation concealment

To avoid spillover effects within the villages, we will conduct a cluster randomised controlled trial using the village as the randomisation unit. Due to the heterogeneity of participants in various disciplines (e.g. gender or educational level), we will use separate randomisation lists for each village (stratified randomisation). Furthermore, for approximate equality of sample size in the study groups, we will use computer generated block randomisation. The study assistants supervising the baseline assessment in the villages will be blinded concerning the group allocation of the village. In addition, group allocation will not be released to the study participants until they provide informed consent, their username, mobile phone number and baseline data. Furthermore, the study assistants conducting the face-to-face interviews at follow up will be blinded when assessing the primary and secondary outcome measures.

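### The named effectiveness test is a pre/post paired t-test, and no listed analysis compares intervention with control or accounts for village

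*Protocol article*

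**What the plan says.** The protocol article describes a randomised between-group comparison. Under Design and main hypothesis: "A two-arm cluster randomised community trial will be conducted to test the efficacy of the mobile coach based intervention". The same section states the primary outcome, improvement in knowledge, awareness and practice, as that "of the intervention group compared to those in the assessment only control group". Randomisation and allocation concealment adds: "we will conduct a cluster randomised controlled trial using the village as the randomisation unit". Sample size calculation recognises the consequence: "As union participants are nested within villages, a potential design effect needs to be considered", and says that "an intra-cluster correlation coefficient of 0.05 could be expected".

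The Data analyses section then assigns the question of effectiveness to one procedure, a paired t-test, which "will be used to examine the effectiveness of the intervention programme by comparing the pre-test and post-test score". Two further inferential methods are listed:

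- "The chi-square test will be worked out to determine the association of the socio-demographic, environmental and behavioural factors with childhood drowning"
- "the risk factors for childhood drowning with socio-demographic, environmental and behavioural factors will be determined using multivariate logistic analysis"

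Neither names study arm as a factor, and no method in the section mentions village. The Outcomes section uses the same before-and-after framing for drowning incidence, which is to be compared between baseline and end line.

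**The concern.** A paired t-test asks whether scores changed over time in the people measured. The hypothesis asks whether they changed more in intervention villages than in control villages. Only the second question uses the randomisation.

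The protocol itself gives reasons to expect change without any intervention effect. The end line survey reuses the baseline instruments, and the Injury surveillance section plans household visits every month in the surveillance areas. Repeat questioning, regular visits about child injury and ordinary change over six months can raise scores in both arms. The control group is there to remove such change, and the named test does not use it for that purpose.

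The paired t-test also treats parents as independent. If parents in one village tend to change together, its standard error is too small even when average scores do not drift. The sample size nearly doubles to allow for this (431 to 840 per group), but the stated analysis does not carry it forward.

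At stake is the main conclusion: a significant pre/post change would be reported as effectiveness even if controls improved just as much.

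**Working it through.** **1. The plan's own figure.** Inputs from Sample size calculation: proportions 0.55 and 0.45, two-sided 5%, power 80%, 10% non-response, ICC 0.05, and m = 20 in the design-effect formula.

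- Unadjusted: [1.96 × √(2 × 0.5 × 0.5) + 0.8416 × √(0.55 × 0.45 + 0.45 × 0.55)]² / 0.10² = (1.386 + 0.592)² / 0.01 = 391.3, so 392.
- Non-response: 392 × 1.10 = 431.
- Design effect: 1 + (20 − 1) × 0.05 = 1.95, and 431 × 1.95 = 840 per group.

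The 840 reproduces. It is sized for a two-group comparison with clustering, and the Data analyses section names no such comparison.

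**2. Does any listed method compare the arms?**

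| Method in Data analyses | Stated purpose | Arm? | Village? |
|---|---|---|---|
| Proportion, mean, SD | level before and after | not stated | no |
| Paired t-test | effectiveness, post against pre | no | no |
| Chi-square | factors associated with drowning | not listed | no |
| Logistic analysis | risk factors for drowning | not listed | no |

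The only two-group test in the article is the chi-square used for sizing. It is based on boys' and girls' drowning proportions and does not reappear as an effectiveness test.

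**3. How often would the paired test reject with no intervention effect?** Let d be a drift common to both arms, in SDs of individual change, with n = 840 parents in the intervention arm. With ICC 0.05 applied to change scores, the paired t statistic is approximately normal with mean d√n and variance DE = 1 + (m − 1) × 0.05. Hence

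P(reject) ≈ 1 − Φ[(1.96 − d√n)/√DE] + Φ[(−1.96 − d√n)/√DE].

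Here √840 = 28.98, so d√n is 0, 2.90 or 5.80 for d = 0, 0.1 or 0.2. Three layouts each give 840 per arm: 42 villages of 20 (the formula's cluster size), 15 of 56 (the village count in Baseline survey) and 5 of 168 (the count in Study settings and population).

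| Villages × parents | DE | d = 0 | d = 0.1 | d = 0.2 |
|---|---|---|---|---|
| 42 × 20 | 1.95 | 16% (16%) | 75% (76%) | 99.7% (99.6%) |
| 15 × 56 | 3.75 | 31% (31%) | 69% (69%) | 98% (97%) |
| 5 × 168 | 9.35 | 52% (54%) | 68% (66%) | 90% (90%) |

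The first figure is from the formula. The figure in brackets is from simulation, 3000 trials per cell. Rejections are two-sided: at d = 0 they split evenly, so about 8% (16/2) to 27% (54/2) would look like improvement. At d = 0.1 and 0.2 nearly all point to improvement, except in the 5-village layout at d = 0.1, where about 6 of the 68 points go the other way.

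**4. The same trials analysed between arms.** A two-sample t-test on village mean changes rejected in 4.2–5.7% of simulated trials across all three layouts and all drift values. A comparison that uses the control arm and respects village therefore holds its 5% level.

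**The case against.** The article is condensed and a separate analysis plan may exist. It does not say in which arm or arms the paired test is run, or that its list of methods is complete. It commits elsewhere to comparison with controls, and the sample size shows that the authors know about nesting. A cluster-adjusted model is the kind of detail an article often leaves out.

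Part of this stands. A reader might infer that the control data will be discarded, or that no between-arm comparison will ever be made. The article does not say so; it shows only that none is listed. The clustering limb is also weaker than the wrong-contrast limb, because silence on a model alone would not be a finding.

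The core does not yield. The article is not silent on effectiveness: it names a test, and that test answers a different question from the hypothesis. Running it separately in each arm does not help, because two within-arm p-values do not test the difference between arms.

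Two stronger numerical readings should also be resisted.

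- With independent parents, the noncentral t for 756 completers (840 × 0.9) gives 78% false rejection at 0.1 SD and over 99.9% at 0.2 SD. That calculation ignores the clustering that is part of the concern, so the clustered figures above are the ones to use.
- An ordinary two-sample test that ignored village would have a true error of 21% at 30 per village, 31% with 15 villages per arm and 52% with 5. The plan does not name that test, so these are not its error rates. At the plan's own design effect of 1.95 the figure would be 16%.

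**Conclusion.** The concern holds. The stated effectiveness test does not address the between-arm hypothesis and ignores the village nesting that the sample size section says must be considered. This is a wrongly stated method, not a detail deferred to an analysis plan, and it must be corrected because the main conclusion depends on it.

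The mismatch needs no numerical assumption; its size does. The drift of 0.1 to 0.2 SD of change is assumed and has no source in the article. The ICC of 0.05 is the article's, but it is not tied to any outcome there, so applying it to change scores is a further assumption. The calculation also takes all 840 parents per arm as analysed. The range across layouts reflects a village count and cluster size that the article does not settle.

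**What to change.** 1. In Data analyses, replace the paired t-test as the effectiveness analysis with a between-arm comparison of six-month knowledge, awareness and practice scores, adjusted for baseline score and accounting for village. Use either a linear mixed model with a random village intercept and small-sample degrees of freedom that the chosen software supports, or, if there are few villages per arm, a baseline-adjusted village-level analysis.
2. Keep within-arm pre/post change as descriptive.
3. Add a stratification term only if Randomisation and allocation concealment is clarified to name a stratum above the village. At present the only stratum named is the village, which is also the randomised unit, so village fixed effects would be collinear with arm.
4. State explicitly that the six-month score is what the between-arm analysis uses, since the article also describes the primary outcome as monthly.
5. Reconcile the End line survey section, which describes the survey as being for intervention areas but covers about 1680 households, the total for both arms. It should say plainly that control villages are surveyed.

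The cost is a rewrite of the analysis wording and a clarification of the end line survey. Baseline and end line scores are already planned. If control villages were in fact not to be surveyed at end line, that fieldwork would have to be added, because no between-arm analysis of six-month scores is possible without it.
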